### Sample size

The aim of the research team is to recruit 50 subjects per group, computing a total of at least 100 participants. The calculation of the sample size takes as its primary outcome intervention efficacy - the reduction of BMI SD scores after the intervention, as specified in a published meta-analytic review of trials [24]. The sample size was calculated in order to detect one BMI SD scores reduction (effect size = 0.60 [24]), according an 80.0% statistical power, 5% significance level to detect differences between groups with two independent samples. It is assumed a 20% dropout rate was estimated.

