		11	Overcome specific barriers	Giving options to eat on specific days (Christmas, restaurants…)	Ticket-aaaa!!! Eating out side!!
		12	Social support and change	Behaviour modification strategies day-to-day	Where are we going next weekend?
		13	Provide instructions about healthier food	knowledge about how to interpret advertising and how buy food	Let’s go to buy!
		14	Provide feedback on performance	Ways in which they can incorporate PA into their lifestyle.	Why do we use the elevator?
		15	Encouragement and setting goals on PA and nutrition	Setting medium-term goals (behaviour strategy session II)	
			Maintaining behaviour strategies		
**3rd Term (April-Mai) Committing and keeping up**	Autonomy (**Reproduction**)	16	Provide knowledge about healthier eating	Learning to make a balanced menu	How do a balanced menu?
		17	Specific encouragement	Relation between PA and food intake	Burning sweets!
			Decisional balance		
	Evaluation (**Motivation**)	18	Self PA evaluation	Evaluating the implementation of PA	How active are we?
		19	Self-Diet evaluation	Evaluating the implementation of Diet	How well you eat?
		20	Encouraging PA and nutrition	Keeping up medium and long-term behaviour (behaviour strategy session III)	
			Maintenance behaviour strategies		
	Closure	21	Enjoying a healthy day together	Closing Party	
**1 each term**	3 weekend extra activities	--	Encouraging active behaviour in an experiential manner and social support	3 extra family physical activities: Ski, FC Barcelona, Aqua party	

The whole intervention will take place in 3 different school centres and health care centres, which have been recruited especially for the intervention and with a strategic localization around the city, in order to facilitate their accessibility. The children’s physical activity sessions will take place using the sport equipments of the school, the theoretical sessions for parents at the same school or at the health care centre next to the school, and the behaviour strategy sessions will be performed in both places. Parents’ and children’s sessions will be performed simultaneously in order to facilitate their attendance. All intervention groups will have a maximum of 15 children and parents.

The 4 structured components are:

a). Physical activity sessions for children

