All physical activity sessions have a similar structure but differ in their contents. Sessions have a four-part structure: assembly, warm-up, workout and cool down periods. During the assembly, the coach explains the day’s training task, attempts to motivate children and introduces contents related to health behaviour based on behaviour change strategies. The assembly’s contents (Table 1) are the same as the family theoretical and practical sessions’ contents for parents, but taught in a playful and experimental atmosphere. Teaching the same health behaviour contents and on the same day and at the same time to both parents and children looks for an improvement in the effectiveness of these contents and their application at home by the family unit. Afterwards, during the warm-up part, dynamic activities such as walking or jogging will be performed at low intensities looking for their activation before the main part. The main part of the session (workout) is primarily focused on being physically active, but as overweight and obese children generally are not especially fit and tend both to be sedentary and tend to have had poor experiences with sport [33], exercises will be planned in short periods of duration such as 4–5 minutes of moderate-high intensity activities intersected by periods of low intensity. Short bouts of intermittent exercise are considered most appropriate for this population [34]. The sessions are also designed looking for their enjoyment through practising and learning different kinds of sports, activities and abilities. Training tasks will be mainly aerobic, but strength, joint mobility and balance will be also included (Table 2). These have been planned according to 3 essential pillars: playing, enjoying oneself and moving in order for children to get rid gradually of their fear and reluctance to sports. The cool-down period is comprised by recovery exercises and static stretching allowing participants to recover.

In addition, each session from the workout part has been planned to be a moderate-high intensity activity. In that sense, one session every two weeks in each centre will be recorded by an accelerometer and heart rate monitor and followed with an assessment in order to be sure that children from the 3 PA centres follow and reach the same indications in terms of intensity.

b). Family theoretical and practical sessions for parents

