#### Counselling group

Each family will be offered 8 individual monthly 10-minute-duration meetings. These sessions will take place at the paediatrician’s office and will be delivered by the child’s nurse or/and paediatrician.

The sessions’ contents will be about tips for the promotion of healthy eating and physical activity habits.

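### The Nereu programme (NP) is delivered in at least four shared groups and counselling individually, but the sample size and named analyses make no allowance for correlation within NP groups

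*Protocol article*

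**What the plan says.** The Nereu programme section describes group delivery at three centres: "All intervention groups will have a maximum of 15 children and parents". Children have 90 one-hour sessions over eight months. Parents meet weekly, also in groups, at the same time. Joint behaviour sessions and weekend activities are added. Counselling is different: "Each family will be offered 8 individual monthly 10-minute-duration meetings".

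The Sample size section plans to "recruit 50 subjects per group, computing a total of at least 100 participants", using a standardised effect of 0.60 and "80.0% statistical power, 5% significance level to detect differences between groups with two independent samples". On attrition it says "It is assumed a 20% dropout rate was estimated". It mentions no group size, ICC or design effect.

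The Statistical analysis plan section lists chi-square or Fisher tests, t or Mann-Whitney tests, a repeated measures analysis, and multiple and logistic regression with adjustment for baseline factors. None of these is given a term for NP group, coach or centre. Healthcare paediatric unit (HPU) appears only as a randomisation stratum, in the Randomization section.

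**The concern.** This is a partially nested design: children are clustered by treatment group in one arm and not in the other. NP children in one group share peers, timetable, venue and a parallel parent group for eight months, and family exchange is part of how the programme is meant to work. If this makes outcomes within a group more alike, 50 NP children carry less information than 50 independent children.

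An analysis that ignores this gives too narrow a confidence interval for NP minus counselling and too high a type I error. A difference that belongs to a few particular groups could then be read as an effect of the programme.

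**Working it through.** **Inputs from the article.** 50 per arm; standardised effect 0.60 (SD set to 1); power 80%; significance level 5%, taken as two-sided because sidedness is not stated; dropout 20%; NP groups of at most 15.

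**Assumptions.** ICC 0.01, 0.05 or 0.10 (not in the documents); groups of equal size; no correlation among counselling children.

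**The plan's own figure.** Under independence, n = 2 × (1.960 + 0.842)² / 0.60² = 43.6, so 44 per arm (45 by the t-test). Dividing by 0.8 gives 55 (57 by t). Multiplying by 1.2 gives 53 (54 by t). A one-sided test needs 35, or 44 after dropout. None of these is 50. Taking 50 as given, 20% dropout leaves 40 per arm, and power under independence is 76.5% (normal approximation) or 75.5% (t-test). This shortfall from 80% comes from dropout, before any clustering.

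**Number of groups.** 50 / 15 = 3.3, so at least 4 groups: 12.5 children each at enrolment, or 10 each with 40 completers.

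**Variance with NP clustering.** With m children per group, the NP design effect is DE = 1 + (m − 1) × ICC. With n per arm, SE² = DE/n + 1/n, so the variance is inflated by VIF = (DE + 1)/2. The naive SE is too small by 1 − 1/√VIF. The true type I error of the naive test is 2 × [1 − Φ(1.96/√VIF)].

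| n per arm, m | ICC | DE | VIF | Naive SE too small by | Type I error |
|---|---|---|---|---|---|
| 50, 12.5 | 0.01 | 1.115 | 1.058 | 2.8% | 5.7% |
| 50, 12.5 | 0.05 | 1.575 | 1.288 | 11.9% | 8.4% |
| 50, 12.5 | 0.10 | 2.150 | 1.575 | 20.3% | 11.8% |
| 40, 10 | 0.01 | 1.090 | 1.045 | 2.2% | 5.5% |
| 40, 10 | 0.05 | 1.450 | 1.225 | 9.6% | 7.7% |
| 40, 10 | 0.10 | 1.900 | 1.450 | 17.0% | 10.4% |

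At ICC 0, DE and VIF are 1 and the type I error is 5%.

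**Power with 40 per arm, effect 0.60.** Two versions are shown. The first applies variance inflation only and keeps the 78 degrees of freedom of the t-test. The second uses Satterthwaite degrees of freedom based on 4 groups: df = (DE/n + 1/n)² / [(DE/n)²/3 + (1/n)²/39].

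| ICC | Power, inflation only | Group-based df | Power with those df | 95% CI width against naive |
|---|---|---|---|---|
| 0 | 75.5% | 11.1 | 69% | 1.10 |
| 0.01 | 74% | 10.4 | 66% | 1.14 |
| 0.05 | 67% | 8.3 | 57% | 1.27 |
| 0.10 | 60% | 6.8 | 48% | 1.44 |

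The ICC 0 row shows that part of the loss in the third and fourth columns is the price of having only four groups to estimate from.

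**How well four groups estimate the group variance.** With 4 groups of 12.5, the ANOVA estimate is zero or negative when an F variable on 3 and 46 df falls below (1 − ICC)/DE. The probability is about 55% at a true ICC of 0.01 (threshold 0.99/1.115 = 0.888) and about 38% at 0.05 (threshold 0.95/1.575 = 0.603).

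**The case against.** **The harm is conditional.** A reader might infer that the intervals are certainly too narrow and the type I error certainly above 5%. The documents do not support that, because they give no ICC. At 0.01 the effect is small, and 11.8% needs both the top of the assumed range and no dropout. Type I inflation also requires that groups still differ when the programme has no average effect.

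**The monitoring is not evidence that groups differ.** A reader might take the accelerometer and heart-rate checks as a sign of real centre differences. Their stated purpose is to ensure that "children from the 3 PA centres follow and reach the same indications in terms of intensity", which is a control on delivery. Common session content and coach training also limit variation. The statement that two coaches run the sessions is ambiguous: if one pair serves every group, coach quality does not vary between groups. Peers, venue and parent group would still be shared.

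**The sample-size phrase proves little.** The words "to detect differences between groups with two independent samples" are the usual name for an unpaired comparison and say nothing deliberate about correlation within an arm. What counts is that the calculation has no allowance for it.

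**HPU may work the other way.** Each of the 16 HPUs supplies both arms, so an analysis that ignores HPU can overstate the SE. Counselling children also share nurses and paediatricians. These points stand. Their size is as unknown as the ICC, so they do not reliably cancel the NP effect, but they are a reason to keep HPU in the model.

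**It may be left to a fuller plan.** The covariance structure of the repeated measures analysis is indeed unspecified, and a separate plan could add a group term. But the article fixes the sample-size basis and names its analyses and adjustment factors, and those make no allowance for group delivery.

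**Conclusion.** The point holds in conditional form. Delivery is nested in the NP arm only, and neither the sample size nor the named analyses account for it. Any positive within-group ICC makes the naive SE too small in the NP arm.

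The size rests on the assumed ICC range of 0.01 to 0.10 and on four equal groups: from a negligible error at the bottom to roughly a doubled type I error at the top, and nothing at ICC 0. The fall to about 75% power at 40 completers per arm is a separate dropout matter and should not be charged to clustering. The change is worth making because it is cheap and because group membership may be hard to reconstruct later.

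**What to change.** - **Data.** Record each NP child's session group and centre. The attendance register described under Adherence may already supply part of this.
- **Analysis.** In the between-arm comparison, use a partially nested model: a random effect for session group in the NP arm only, counselling children as singletons, small-sample (for example Satterthwaite) degrees of freedom, and HPU kept as a stratification factor.
- **Sensitivity.** Because the group variance will often be estimated as zero, report alongside it confidence intervals at a range of fixed ICCs, for example 0.01, 0.05 and 0.10. A single fallback value would be arbitrary and often invoked.
- **Sample size section.** State that the planned power assumes no clustering within NP groups. Add that, with 40 completers per arm and an effect of 0.60, power would be about 74, 67 and 60% at ICC 0.01, 0.05 and 0.10 from variance inflation alone, or about 66, 57 and 48% with group-based Satterthwaite degrees of freedom.

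**Cost.** Two data fields, one model term and a short statement. The statistical price is real: with 40 per arm and the small-sample degrees of freedom, the confidence interval is about 14 to 44% wider over that ICC range.

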#### Counselling group

Each family will be offered 8 individual monthly 10-minute-duration meetings. These sessions will take place at the paediatrician’s office and will be delivered by the child’s nurse or/and paediatrician.

The sessions’ contents will be about tips for the promotion of healthy eating and physical activity habits.

#### Measurements

As the intervention is principally focused on a family-based behavioural multi-component intervention for children’s obesity, both children and parents will be assessed. The main measure parameters are described in Table 3.

**Table 3 T3:** Measurements

**Aim**		**Nereu and Counselling group measures**	
		**Children**	**Parents**
Cardiovascular risks factors	Anthropometry	Weight	Weight and Height
		Height	
		BMI z score	
		Waist circumference	
		Waist-size index	
		Triceps skinfold	
		Subscapular skinfold	
	Blood pressure	Diastolic and systolic pressure	NOT analysed
	Blood test	Cholesterol (LDL, HDL), triglycerides, glucose, insulin, TSH and cortisol ^1^	NOT analysed
Physical condition	Physical condition	ALPHA test set [42]	
Behaviours	Physical activity	Seven-days Accelerometry	International Physical Activity Questionnaire IPAQ [74]
		Seven days recall physical activity questionnaire (PAQ-C) [46]	
	Nutrition	24 h dietary recall (x 3 days)	Frequency consumption (CFCA –adults version)
		Frequency consumption (CFCA – children version)	
Psychological aspects	Physiological, physical and cognitive	Physical activity self-efficacy [64]	Health-specific self-efficacy [82]
		Physical self-concept (MIFA) [66]	
		Body-image: Figure Rating Scale [67]	
		Physical activity enjoyment (PACES) [69]	
Health related quality of life	HRQOL	PedsQL 4.0 [70]	
Health economic data	Cost-effectiveness	CHU 9D [73]	EQ-5D EuroQol Group [84]
Modifiers variable	Pubertal maturity	Tanner pubertal stage [88]	
	Socio-economical and demographic parameters	Some questions from de National Healthy Survey for children [89] and for parents [90]	
	Adherence	Attendance log	
	Satisfaction	Survey	

^1^the measurement will be undertaken 2 times: at baseline and at the end of the intervention.

Measurements will be assessed before and at the end of the intervention, and 6 and 12 months after the end of it.

### Children’s outcome

#### Anthropometry

Anthropometric parameters will be measured using standard practice: weight will be measured to the nearest 0.1 kg using an electronic scale (Tanita Model SECA 214, Hamburg, Germany) and height (Ht) to the nearest of 0.1 cm with a stadiometer (Seca 214, Hamburg, Germany) with children lightly dressed and barefoot. The BMI will be calculated as weight (kg) divided by squared (m^2^) height and standard deviation score (BMI SD score) will be determined from the LMS method [40]. Waist circumference (WC) will be measured in centimetres with an anthropometric tape (precision: 0.1 mm), placed horizontally at the level of the maximum abdominal protrusion at the end of a gentle expiration [30]. Waist-to-height ratio (WHtR), will be calculated as waist circumference (cm)/height (cm).

Triceps and subscapular skinfold thickness will be measured at the right side of the body with the child standing up, with a Holtain skinfold calliper (Holtain, Crymych, United Kingdom) to the nearest 0.2 mm. Triceps skinfold is a vertical fold measurement performed on the posterior midline of the upper arm, half way between the acromion and the olecranon processes. Subscapular skinfold measurents will be taken about 20 mm below the tip of the scapula diagonally (at 45º angle to the lateral side of the body). Both skinfold measurements will be performed with the arm held freely to the side of the body. Waist circumference and skinfold measurements will be done in order (not consecutively; rotating sites) and repeated three times.

#### Blood pressure

Blood pressure assessment will be performed at the level of the brachial artery of the dominant arm using an automated (i.e. oscillometric) device (Omrom) with children in a relaxed sitting position, after 3 minutes of rest. Measurements will be taken in duplicate and the last of both measurements will be recorded.

To determine hypertension, the normative values from Spanish children published by Fernández-Goula, et al. [41] will be used.

#### Blood tests

With the participants in the sitting position, blood samples will be drawn by venipuncture after an overnight fast. These samples will be used to assess cholesterol (LDL, HDL), triglycerides, glucose, insulin, TSH and cortisol levels. Blood samples will be analysed with an automated method at the laboratory of the Hospital Universitari Arnau de Vilanova, in Lleida.

#### Physical condition

To evaluate physical activity and fitness levels, children will perform the ALPHA fitness test battery [42]. The ALPHA fitness test was specially created to assess the health-related fitness status in children and adolescents within the European Union. The physical measurements of the ALPHA fitness test that will be measured from the children are: handgrip strength, standing long jump and 4 × 10 m shuttle run test. Procedures will follow the standard guidelines indicated in the test manual [42]. To measure their aerobic capacity, the 6-minute walk testwill be used [43]. This test has been validated and has shown reproducibility in obese children [43].

#### Sedentary and physical activity behaviours

Sedentary and physical activity behaviours will be assessed by means of a) the objective measurement of physical activity levels during seven days and b) the filling in of a self-report activity questionnaire.

The objective measurement of physical activity level will be done using ActiGraph GT3X + accelerometers (ActiGraph, Pensacola, EEUU). Accelerometers will be worn by participants all day for eight consecutive days; however data from the first day will be discarded for analysis. Accelerometers will be placed on a small elastic belt and positioned on the waist. Data will be collected and stored in 30-second epochs and the mean activity counts per minute will be calculated and analyzed with ActiLife 6.0 software application (ActiGraph, Pensacola, EEUU). Age and gender specific cut-off points will be used to categorize behaviours into sedentary, light, moderate and vigorous intensity activity [44]. Before its placement, a researcher will give oral and written information about the procedure to the children and family. Families will be given a contact telephone number in case of problems during the period.

Additionally, on the day of the accelerometer is removed, children will fill out the Spanish version [45] of the Physical Activity Questionnaire for Children (PAQ-C) [46]. This is a self-administered questionnaire that assesses physical activity levels in children during the last 7 days ofthe school year [46]. The PAQ-C is one of the most widely used questionnaires of physical activity level assessment and its internal consistency and validity for children has been well established [47-50]. The PAQ-C provides a summary physical activity score derived from 9 items, each scored on a 5-point scale, which is designed to collect children’s information about different physical activities and moments: (1) spare time activity, (2–8) physical education, recess, lunch, right after school, evening, weekends, and describes-you-best, (9) take the mean of all days of the week. Questionnaires will be analysed using the scoring of the PAQ manual [51].

#### Dietary behaviour

To assess and monitor the dietary status of participants, a dietary 24 h-intake-recall for three days and an eating frequency questionnaire will be performed.

The dietetic record will be done for three days, in which the families will annotate what the child has eaten during these days. It will cover two weekdays and one weekend day, and later a nutritionist will help them to interpret their annotations and power as recorded in the program by means of the quantitative dietary diary proposed by Burke, as shown by Martin-Moreno [52] revisited and updated by Willet [53,54]. Families will be individually taught how to fill out the dietary 24 h-intake form, before they carry it out at their own home.

On the other hand, children will also complete the eating frequency questionnaire CFCA [55]. The questionnaire consists of a list of nutrients or group of nutrients. Children will be asked to indicate the intake frequency (daily, weekly or monthly) of each component of the list. This may be considered as a report card on the overall quality of diet consumed. However, if the information is combined with quantitative data about mean portions, the assessment could be semi-quantitative [56-58]. This method has already been used in longitudinal nutritional studies in children [59,60] and to assess eating patterns in children [61]. Both questionnaires are included in the diet assessment survey developed by Burke and have been performed in longitudinal studies of large populations of different ages [62]. The combination of both methods has also been applied to the assessment of eating patterns in Spain [63]. Both questionnaires will be conducted by a trained/experienced interviewer.

#### Psychological aspects and physiological factors

The physical activity self-efficacy for children [64] will be used to provide a self-report of their PA self-efficacy. The scale is a specific Spanish scale that consists in 12 items and a dichotomous scale (yes or no) will be used instead of the five-point scales commonly used for this type of instruments in order to facilitate their understanding to children [64]. The Cronbach alpha consistency is .733 and test-retest reliability is .867 [64].

The physical self-concept of children will be measured with the physical self-concept scale (MIFA) by Moreno [65], as a predictor of the intention of being physically active. It is the Spanish version of the physical activity enjoyment scale [66]. It is a questionnaire composed by 5 items, especially created for children in order to know their intention to be physically active after school. The response scale is a Likert scale ranging from 1 (strongly disagree) to 5 (strongly agree).

Body image will be assessed using the Body Figure Perceptions by Collins [67]. This instrument is useful to investigate body figure perceptions and preferences among young children [67]. This measure consists in seven gender-specific line drawings of increasing size, labelled from 1 (thinnest figure) to 7 (heaviest figure). There is a specific figure for boys and girls.

Evaluation of the physical activity enjoyment will be measured according to the Spanish version [68] of the physical activity enjoyment scale (PACES) [69]. The questionnaire consists in 16 items rated from 1 (strongly disagree) to 5 (strongly agree). The PACES is for a single enjoyment factor that can be negative or positive. The results found by Moreno [68] revealed that the scale is a valid and reliable tool to measure sport enjoyment in Spanish population.

